## Abstract

**Background:**

Despite two decades of interventions, rates of sexually transmissible infections (STI) in remote Australian Aboriginal communities remain unacceptably high. Routine notifications data from 2011 indicate rates of chlamydia and gonorrhoea among Aboriginal people in remote settings were 8 and 61 times higher respectively than in the non-Indigenous population.

**Methods/design:**

STRIVE is a stepped-wedge cluster randomised trial designed to compare a sexual health quality improvement program (SHQIP) to usual STI clinical care delivered in remote primary health care services. The SHQIP is a multifaceted intervention comprising annual assessments of sexual health service delivery, implementation of a sexual health action plan, six-monthly clinical service activity data reports, regular feedback meetings with a regional coordinator, training and financial incentive payments. The trial clusters comprise either a single community or several communities grouped together based on geographic proximity and cultural ties. The primary outcomes are: prevalence of chlamydia, gonorrhoea and trichomonas in Aboriginal residents aged 16–34 years, and performance in clinical management of STIs based on best practice indicators. STRIVE will be conducted over five years comprising one and a half years of trial initiation and community consultation, three years of trial conditions, and a half year of data analysis. The trial was initiated in 68 remote Aboriginal health services in the Northern Territory, Queensland and Western Australia.

**Discussion:**

STRIVE is the first cluster randomised trial in STI care in remote Aboriginal health services. The trial will provide evidence to inform future culturally appropriate STI clinical care and control strategies in communities with high STI rates.

**Trial registration:**

Australian and New Zealand Clinical Trials Registry ACTRN12610000358044

## Background

For almost two decades sexually transmissible infection (STI) diagnoses have occurred at hyperendemic rates in many remote Australian Aboriginal and Torres Strait Islander (hereafter referred to as ‘Aboriginal’) communities [1]. Data on prevalent and incident infection in these settings are derived from routine notifications reportable by public health agencies and sporadic prevalence surveys conducted in the context of screening programs [2].

In 2011 the diagnosis rates of *Chlamydia trachomatis* (chlamydia) and *Neisseria gonorrhoeae* (gonorrhoea) among Aboriginal people resident in remote communities were 8 and 61 times greater than in the non-Indigenous population [1]. A similar situation exists for *Trichomonas vaginalis* (trichomonas) in the Northern Territory, the only jurisdiction which requires notification of this infection [3]. The majority of these three STIs are notified among people aged 15–29 years [1].

While differential patterns of testing may play some role in these discrepant rates of diagnosis, a major component of the disparity [1] is almost certainly attributable to inadequate access to early detection and appropriate treatment programs offered in primary health care settings [4].

Chlamydia, gonorrhoea, and trichomonas are fully curable STIs but are often asymptomatic for long periods and can lead to serious complications if untreated [5]. For example, untreated chlamydia infection may potentially cause pelvic inflammatory disease (PID), ectopic pregnancy and tubal factor infertility among women [6,7]. In the Top End of the Northern Territory, 26% of all Aboriginal women were found to have had history of PID [8]. Chlamydia can also result in adverse pregnancy outcomes including premature labour and birth, low birth weight, intrauterine growth restrictions, postpartum endometritis [9,10] and a range of neonatal infections including infectious conjunctivitis and pneumonitis [5]. Gonorrhoea has similar sequelae to chlamydia and can also lead to disseminated infection [5]. Trichomoniasis among women is associated with premature rupture of membranes, premature delivery and low birth weight [11,12] while trichomoniasis in men is an important cause of non gonococcal urethritis and is associated with prostatitis [13,14]. All three STIs are associated with an increased risk of HIV transmission [15,16].

### STI programs in remote aboriginal communities

Despite many years of effort aimed at reducing the incidence and prevalence of STIs in remote communities, it is speculated that increased support to primary care is required to achieve best practice in the clinical management of STIs. In this setting, staff turnover is high and the burden of chronic disease, other infectious diseases, and child and maternal health needs is particularly high [17,18]. Given that resources are finite, particularly in regard to the availability of clinical personnel, several approaches have been used to support specialised areas of health service need in remote communities. One method has been to appoint specialist visiting personnel to provide service delivery in primary care settings at a regional level, focusing exclusively on the area of need [2,19,20]. These activities are recognized as having the fundamental limitation that they are unlikely to be well enough resourced to provide specialised assistance to all, or even a high percentage, of clinical episodes. In the area of sexual health, population screening has been used in some communities to improve testing coverage, but generally these programs depend on outside teams providing a service within a limited time frame, and may not always contribute to the confidence and competence of local clinical staff.

In addition to detecting and treating infections, a major goal of improving sexual health service delivery is to reduce the overall prevalence of infections. Analyses of program data to compare changes in STI prevalence over time in communities with different levels of service activity provide some insight into the effectiveness of programs [2], but their interpretation is compromised by a number of potential confounding effects. These effects include differences between communities, such as size and mobility of the population, sexual networks and the extent of treatment-seeking behaviours [2], all of which are difficult to monitor systematically. Another approach is to randomly allocate selected communities to receive a program of support over a defined time period to enhance STI diagnosis and treatment to best practice levels and to compare outcomes with control communities. This approach has been trialed in remote primary health care services addressing improvements in quality of care related to chronic disease [17,21-23].

The primary objectives of the STRIVE trial are:

1. To determine whether targeted support to health services can achieve substantive and sustained improvements in the provision of sexual health clinical services in remote Aboriginal communities; and

2. To determine whether the attainment of best practice levels in clinical activity can reduce the prevalence of curable STIs in these communities.

## Methods

### Study design

STRIVE is a community-based stepped-wedge cluster randomised controlled trial. During the first 18 months of the trial, 24 ‘trial clusters’ comprising 68 remote communities and primary care centres in Central and Northern Australia were recruited to participate in the trial, and undergo preparatory procedures. The trial clusters are the unit of randomization and comprise either a single community or several communities that share close cultural affinities and/or are geographically proximal. The clusters were determined by the research team in consultation with stakeholders and are located in remote Australia, in the Northern Territory (18 clusters), Western Australia (3 clusters) and Queensland (3 clusters).

At the start of each of the three years, one third of the clusters are randomly assigned to receive the SHQIP (see Figure 1). Clusters not randomised to receive the SHQIP continue to undertake usual STI care. By the start of year four, all clusters will be receiving the SHQIP.

**Figure 1 F1:**
[figure not shown]
STRIVE study process.

The stepped-wedge design [24] ensures that all communities and their health services in the trial receive the SHQIP. Given that this design enables the intervention to be delivered to all clusters and that the intervention is likely to have a potential beneficial effect [25] it was affirmed as a preferred model with key stakeholders.

Chlamydia, gonorrhoea and trichomonas are good candidates for clinical quality improvement strategies because they are endemic in remote Aboriginal communities and can be easily diagnosed and treated. Moreover in the same communities infectious syphilis [26] and donovanosis [27] have declined significantly over the last decade as a result of sustained and specific targeted clinical programs. While STRIVE focuses on the three specified STIs, it also encourages ‘best practice’ for the detection and treatment of all STIs.

### Ethics and informed consent

During 2009–2010 the STRIVE study protocol was approved by the Central Australian Human Research Ethics Committee, the Cairns and Hinterland Human Research Ethics Committee, the Human Research Ethics Committee of the Northern Territory Department of Health and Menzies School of Health Research, the University of New South Wales Human Research Ethics Committee, the Western Australian Aboriginal Health Information Ethics Committee, and the Western Australian Country Health Service Board Research Ethics Committee.

Participating health services signed a site participation agreement prior to commencement of their involvement in STRIVE. Consultation and laboratory data are collected through routine patient management systems.

### Community engagement and collaborations

A key underlying principle of STRIVE is effective engagement at all stages with stakeholders including government, non-government organisations and the community. Extensive community engagement occurs through multiple modes including engagement with key stakeholders, an initial community engagement workshop and constant communication with participating health services.

### Identification of communities and health services and eligibility criteria

For inclusion in STRIVE, communities must be considered remote by the Australian Bureau of Statistics [28]; have a resident population of at least 100 Aboriginal people aged 16–34 years and Aboriginal people must comprise a majority of the population; have a health service willing to participate based on the trial protocol including an ability to provide access to de-identified clinical data throughout the trial. Study personnel determined eligibility of communities and health services to participate. All eligible communities and health services within each trial cluster were invited to participate. Conversely a community is not eligible if there are multiple health services in that community.

### Randomisation

Towards the end of the preparatory period, eight trial clusters (designated “first year trial clusters”) were randomly selected to receive the SHQIP in the second year. Towards the end of the second year of STRIVE, a further eight trial clusters were randomly allocated to the SHQIP in the third year and fourth years.

Randomisation occurs after participation agreements have been signed and the baseline STI prevalence survey has been conducted. Trial clusters are randomised to the SHQIP or usual care using a minimisation approach that aims to balance population testing coverage rates, cluster population size and geographic region across the baseline levels in each trial cluster. The statistician, who was blinded to the study sites (regions), prepared the randomisation list for each geographical area. The protocol was implemented in four regions of Australia in mid 2010.

### Baseline activities conducted with participating health services

At enrolment, all participating primary care services undertake three preparatory steps, supported by one of the STRIVE study coordinators, each of whom works on a regional basis. Step 1 is a site assessment to provide information on the health service context (staffing, location, pathology provider, patient information management system) and both current and past sexual health activities; Step 2 involves the development and installation of an upgraded STI template within the service’s patient information management system. Step 3 involves provision by the coordinator of training and support to conduct a STI prevalence survey with the service.

### The sexual health quality improvement program (SHQIP)

The SHQIP is the intervention that takes place at each health service, beginning in the year that the cluster to which it belongs is selected by the randomisation process. It is a multifaceted program, that involves an annual assessment covering six key areas considered as STI best practice (a systems assessment) followed by the development of an action plan, both undertaken with the support of a STRIVE coordinator. At six-monthly intervals, the service (both management and clinical staff) receives quantitative reports from patient information systems and laboratory data on clinical activities based on a set of quality indicators (see Table 1) and participates in collaborative feedback meetings with STRIVE coordinators to review and address needs in sexual health clinical service delivery. The coordinators also identify and address requirements for training in sexual health service delivery. Services assigned to the SHQIP receive a one-off payment of $2,000 to support health promotion activities aimed at increasing clinical visits for STI testing by young people, and at six monthly intervals they receive payments calculated on the basis of their performance against the best practice indicators (described below).

**Table 1 T1:** STI best practice indicators

**STI best practice indicators**	**Target**
Proportion of Aboriginal patients aged 16–34 years old who have an annual test for chlamydia, gonorrhoea and trichomonas	80%
Proportion of health service patients presenting with STI symptoms who receive immediate treatment	95%
Proportion of people diagnosed by laboratory test with chlamydia, gonorrhoea or trichomonas who are treated within seven days of the test result being received from the laboratory	80%
Proportion of patients found by laboratory test to have chlamydia, gonorrhoea or trichomonas who have a test for re-infection at between two to four months following treatment	80%
Proportion of named sexual contacts, of people found to have chlamydia, gonorrhoea or trichomonas, tested and treated	50%

#### Systems assessment

STRIVE coordinators work collaboratively with health service staff to assess the current status of sexual health service delivery using a self-assessment tool based on the methods of the Audit and Best Chronic Disease Extension program [29], The tool enables any gaps in STI care and management to be identified, and explores ways to improve sexual health clinical services in relation to the diagnosis and management of STIs. The systems assessment covers six areas; including health hardware, clinical services, information systems, health promotion, organisational commitment, surveillance and evaluation. Staff score their health service on an 11-point scale in each area, with an aim of improving areas at subsequent annual assessments. The areas cover the fundamental components of a comprehensive sexual health program identified for the remote primary health care setting [30].

### Best practice STI indicators

The indicators established for STRIVE (Table 1) are based on current guidelines for best practice in STI care and management [31-33]. According to these guidelines, young people at risk of STIs should have a test for chlamydia, gonorrhoea and trichomonas every year; syndromically treated at consultation, and as soon as possible following a laboratory diagnosis. Those treated for an infection(s) should be asked to refer or name sexual contacts to clinic staff, and return for a test for re-infection for gonorrhoea and chlamydia at three months. The indicators in Table 1 are discussed with health service staff at the first systems assessment meeting, and form the basis for subsequent reports on performance. Each indicator is calculated for six month periods, apart from the annual screen. Indicator calculations are based on Aboriginal residents as determined by the health service.

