#### Indicator reports

Health service staff and managers are provided with six monthly reports based on the best practice indicators, to discuss at the feedback meetings. These quantitative reports show the extent of improvements towards the targets. In addition to the best practice indicators, the reports also provide information on the proportion of community residents in the target age group who attended the health service during the period. Population denominators are derived from the number of Aboriginal residents who attended the health service in the preceding two years.

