#### Clinical performance payments

After randomisation to the SHQIP, health services receive incentive payments on a six monthly basis, except for testing coverage, which is assessed annually. Payments are calculated on the basis of progress towards best practice targets. Services receive payments of $100 (AUD) for each episode of treating patients with STI symptoms at consultation; for treating a person diagnosed with an STI within seven days of the laboratory result being received at the clinic; and for re-testing each individual diagnosed with an STI at three months. Services also receive $100 per contact tested and treated within two weeks of being named. For a 10% or more improvement in any indicator in the subsequent period, the service receives a $500 payment. Services which reach the targets receive an additional $500, once only.

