### Outcome measures

Primary outcomes are:

1. Prevalence of chlamydia, gonorrhoea or trichomonas in male and female Aboriginal residents aged 16–34 years, as measured using the trial prevalence assessment (Table 2); and

2. Performance in clinical service activity based on the best practice indicators over the period of the trial (Table 1).

All outcomes will be calculated by cluster, service, gender, patient age group (16–19, 20–24, 25–29, 30–34 years), STI type, and the reason for attendance.

Secondary outcomes are:

1. Diagnoses of pelvic inflammatory disease (PID) and epididymitis

2. Feasibility and acceptability of research conducted in remote primary care settings.

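### Services that know their allocation decide who counts as resident for primary outcome 2, so reclassification after the switch to SHQIP could raise the indicators without any change in care

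*Protocol article*

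**What the plan says.** - **Who counts.** Best practice STI indicators: "Indicator calculations are based on Aboriginal residents as determined by the health service".
- **What it feeds.** Outcome measures makes performance on the Table 1 indicators over the trial the second primary outcome.
- **Limit on the denominator.** Indicator reports: "Population denominators are derived from the number of Aboriginal residents who attended the health service in the preceding two years".
- **Who is paid.** Clinical performance payments: "After randomisation to the SHQIP, health services receive incentive payments on a six monthly basis", with testing coverage assessed annually instead. The general basis is: "Payments are calculated on the basis of progress towards best practice targets".
- **Payments per event.** "Services receive payments of $100 (AUD) for each episode of treating patients with STI symptoms at consultation", and the same amount for treatment within seven days of a laboratory result and for each re-test at three months. For contacts: "Services also receive $100 per contact tested and treated within two weeks of being named".
- **Payments on a proportion.** $500 for an improvement of 10% or more in an indicator, and a single $500 for reaching the targets.
- **Contact indicator.** Table 1: "Proportion of named sexual contacts, of people found to have chlamydia, gonorrhoea or trichomonas, tested and treated", target 50%.
- **Data.** Table 2 has testing and management data, with associated demographics, extracted every six months from all services, whichever arm they are in.

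The SHQIP section makes the six-monthly reports and the payments part of the intervention, so services in usual care receive neither.

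**The concern.** Residency helps define the denominators of a primary outcome. The people who settle it work in the service, know whether the service is in SHQIP, and after the switch are shown the resulting proportions and rewarded in part on them. A service in usual care has the same discretion but not the same prompt to use it.

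No bad faith is needed. The action plan section gives regular data review and electronic recalls as examples of SHQIP strategies. Staff who chase an unanswered recall may reasonably mark the person as having moved away, and that person is by definition untested or not re-tested. The Background lists population mobility among the features of communities that are hard to monitor systematically. Even where each removal is correct, a list cleaned in one arm and not in the other makes the two proportions non-comparable.

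Such an effect starts at the switch, so randomisation does not remove it. Both main analyses (first against second round after one year, first against third round after two years) would carry it as apparent benefit.

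**Working it through.** The article states no expected rate, power or sample size for the second primary outcome, so there is no figure of the plan's own to reproduce. The check has three parts.

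**1. Which payments can respond to the denominator**

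| Indicator | $100 per event | $500 for improvement or target |
|---|---|---|
| Annual test | none listed | yes |
| Symptomatic treatment | yes | yes |
| Treatment within seven days | yes | yes |
| Re-test | yes | yes |
| Named contacts | yes | yes |

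Per-event payments gain nothing from removing people. For annual testing, the only itemised payments that apply are the two that depend on a proportion. It is also the indicator whose denominator rests most directly on the resident population.

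**2. How far selective removal moves a proportion**

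Let p be the true proportion and d the share of the denominator dropped, all of them people who did not meet the indicator (worst case). The apparent proportion is p/(1 − d). The values of p and d are assumptions.

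| p | d = 5% | d = 10% | d = 20% | d needed for +10 points |
|---|---|---|---|---|
| 20% | 21.1% | 22.2% | 25.0% | 33% |
| 30% | 31.6% | 33.3% | 37.5% | 25% |
| 40% | 42.1% | 44.4% | 50.0% | 20% |
| 60% | 63.2% | 66.7% | 75.0% | 14% |

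- For a 10% relative rise, 1/(1 − d) = 1.10, so d = 1 − 1/1.10 = 9.1%, whatever p is.
- For a 10-point rise, d = 1 − p/(p + 0.10), the last column.
- If removal is unrelated to meeting the indicator, the expected proportion does not change.

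In assumed counts, take 300 residents with 90 tested (30%). Removing 42 of the 210 untested gives 90/258 = 34.9%, a rise of 4.9 points or 16% in relative terms (34.9/30 = 1.16). A 10-point rise needs 90/225 = 40%, that is 75 of the 210 untested removed (36%). The article does not say whether its 10% is relative or absolute. The 4.9-point shift would earn the improvement payment only on the relative reading, but it distorts the trial outcome on either.

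**3. The contact proportion**

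With 20 contacts tested and treated (assumed), 60 recorded names give 20/60 = 33% and 40 give 20/40 = 50%, the target. Going from 60 names to 40 raises the indicator, and going from 40 to 60 lowers it, for the same 20 people reached. The direction depends on how many names are elicited and recorded.

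**The case against.** The strongest reply has five parts.

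- **Most of the money follows counts.** Four of the five indicators carry a $100 payment per event, and removing someone who met the indicator could lose that money. This stands, and it weakens the incentive for those four. It does not help annual testing, which has no per-event payment.
- **The attendance rule and the data sources limit discretion.** Denominators are tied to attendance in the preceding two years, and data come from patient systems and laboratories. This stands as a limit, but resident status among those attenders is still the service's decision.
- **The discretion exists in both arms.** True: usual-care lists can drift too. The difference between arms lies in reports, payment and data review, not in who decides.
- **No rate of reclassification is given.** True, so the size cannot be stated, only illustrated.
- **An article condenses the full protocol.** A freeze or audit rule may be written elsewhere, and its absence here proves nothing. The point does not rest on that absence: it rests on the rule the article does state, which assigns residency to the service.

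A reader might go further and infer that services also choose which contacts count as named, and so can push that indicator up. The article does not support this. Treated patients are asked to name contacts or refer them, the residency sentence does not cover contacts, and $100 per contact rewards finding more of them. Staff influence the count by asking and recording, with no fixed direction.

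**Conclusion.** The residency rule leaves the second primary outcome open to differential ascertainment. Selective reclassification of untested or un-retested people after the switch could inflate the indicators in SHQIP clusters, with annual testing coverage the most exposed.

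The magnitude is unknown. The 9.1% figure is a worst case: it assumes that everyone dropped had not met the indicator and that comparison clusters lose no one in the same way. It shows that a modest change in a list can matter, not that one will occur.

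It would be tempting to conclude that the indicators will be inflated, and in one arm only. The documents do not support that: only the reports and payments are confined to SHQIP services, and nothing shows how often status is changed in either arm. The first primary outcome, prevalence, comes from a separate assessment and is outside this point.

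**What to change.** 1. **One rule for the trial outcome.** The trial team applies the same residency definition to the six-monthly extracts in all 24 clusters: attendance in the preceding two years, plus resident status as recorded in the extract at or before the start of the period. No one leaves the denominator because of a status change within the period. The feedback reports can keep the service's own view.
2. **Sensitivity analysis.** Fixing status within a period does not undo removals made in earlier SHQIP periods, which matters most for the two-year comparison. Repeat the analysis with status from the last extract before the cluster's switch, and from the same calendar time for its comparison clusters.
3. **Contacts.** Keep the named-contact proportion, and report beside it contacts named per index case and contacts tested and treated per index case, so that a change in names recorded can be seen.

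The cost is small if the extracts hold resident status with a usable date. The article mentions demographics but does not list that field, so it needs confirming; an address field should not be assumed. Some people who truly moved away will stay in the denominator, so absolute coverage will be slightly lower. The sensitivity analysis also leaves out people first recorded after the switch.
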